## Sample Leaflet (Print health message)

[figure not shown]

### Maternity Waiting Home

#### Have you ever heard about maternity waiting home?

**Maternity waiting home** - is a shelter where pregnant women in last weeks of gestation can await their delivery and be transferred to a nearby medical facility shortly before delivery, or earlier should complications arise.

#### When should woman stay at maternity waiting home?

- ◇ Pregnant woman stays at maternity waiting home in last weeks of pregnancy.
- ◇ Health care professionals can give a woman information about when to go to maternity waiting home.

### Benefits of Maternity Waiting Home

- ◇ To avoid maternal problems caused by travelling long distances during labour
- ◇ To receive close medical follow-up in last weeks of pregnancy
- ◇ To stay near health facility and receive medical care during labour and delivery
- ◇ To be easily transferred to health facility for labour and delivery, or should complications arise
- ◇ It is Safe and comfortable place for pregnant woman to stay before delivery
- ◇ It allows woman to network with others and learn how to care for herself and the baby

[figure not shown]

**Can male partners (husbands) involvement improve maternal health?**

Male partners involvement during pregnancy and child birth can improve maternal health outcomes.

**What does male partners involvement mean?**

Male partners involvement refers to husbands engagement in maternal health issues. Maternal health can not be ensured without male partners participation.

- ⇒ Do you support your wife?
- ⇒ What kinds of support do you provide to your pregnant wife?

Male partner's (husband's) support is essential during pregnancy and child-birth.

Kinds of support a husband provide to his pregnant wife are:

⇒ **Social support**

Example: Taking care of children, household care and/or other work

⇒ **Financial support**

Example: cover costs for transportation to health facility, food & medications

⇒ **Emotional support**

Example: Exercise free couple-communication, accompany his wife when she goes to health facility for medical care, encourage her to be strong while she feels discomfort, and/or decide to use health facility for delivery

[figure not shown]

A woman attending ANC with her husband

### Tips for husbands

#### What to do?

- ⇒ Communicate with your wife freely about reproductive health matters
- ⇒ Support your wife by sharing household responsibilities such as taking care of children
- ⇒ Cover transportation and medication costs when she visit health facility
- ⇒ Accompany her when she goes to health facility for ANC visit
- ⇒ Show her sense of empathy when she feels any discomfort
- ⇒ Do plan of maternity waiting home use with your wife
- ⇒ Do plan of labour and delivery with your wife

## Reporting format [CONSORT Flow Diagram]

The study findings will be reported using Consolidated Standards of Reporting Trials (CONSORT) for cluster randomized trials criteria  (Figure 1).

[figure not shown]

**Figure 1:** CONSORT Flowchart

## **Usual standard of care**

Preventive and promotive health services are provided to the community in the study setting through rural health extension programs. The rural health extension program packages include disease prevention and control, family health, personal hygiene, environmental sanitation, health education, and communication. Consequently, under the family health package, rural health extension workers promote contraceptive use, antenatal care, institutional birth, and other family health issues. These services are common to all households in the study setting. Other than these usual services, the control group will not receive the basic components of current intervention, such as group health education and home visits, which aim to educate and counsel women and their male partners together regarding paternal support and MWH use. The control group will receive the current intervention after the completion of the study through routine rural health extension programs.

## **Available MWH services**

Women who stay at MWHs will receive the services based on the national guideline. The women will be registered and provided sleeping rooms at their arrival. The antenatal check-ups and follow up by health professionals are the basic available health services. The MWH staff will be informed to welcome the male partners of the pregnant women and encourage them to support their spouses during their stay at the MWHs. In addition to the registration book at the MWH, a separate registration format will be prepared for this study purpose.

## **Compliance parameter**

The number of participants who attended health education at baseline and contacted at the two home visits will be used to determine the participants' compliance with the intervention. We will use attendance sheets to determine participants' compliance with the proposed intervention packages. However, for various reasons, the participants in the intervention may not comply with the intervention. This may have undesirable effects on women's use of MWHs. This will be considered a dose-response function during the data analysis (Table 2).

**Table 2:** Summary of the trial protocol

| Content of intervention                  | Dosage  | Frequency | Duration | Compliance parameter                                   |
|-------------------------------------------------|----------------|------------------|-----------------|---------------------------------------------------------------|
| Group health education at baseline and leaflets | 90-120 minutes | Once             | One month       | Number of participants attended the health education sessions |
| Home visits and leaflets                        | 30-45 minutes  | Twice            | Two months      | Number of participants contacted at home visits               |

### **Primary outcome**

The proportion of MWH use among participants will be measured. The use of MWH can be traced through individual surveys and MWH record reviews. The proportion of MWH use will be calculated for each trial arm at baseline and end line. The effectiveness of the intervention will be measured as a difference-in-differences in the proportion of MWH use between the trial arms.

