## Sample size calculations

The Hooper and Bourke method for cluster randomization studies of parallel arms with repeated cross-sections is used to calculate the sample size. To illustrate within intraclass correlation coefficient (ICC) and between ICC, the technique comprises the measurement of two design effects, with the product of the two being used to inflate the sample size for individual randomization. The within ICC is the correlation between any two pregnant women in the same cluster, while the between ICC is the correlation between any two pregnant women in different clusters. The first design effect ( $d_c$ ) attributable to cluster randomization is measured using a within ICC of 0.05 obtained from a community-based cluster randomized trial in Ethiopia. The design effect ( $d_c$ ) is calculated as:

$$d_c = 1 + (m - 1)\rho$$

Where  $m$  is the cluster size assumed to be 20 (i.e., the total number of pregnant women who will be questioned in each cluster) and  $\rho$  is the within ICC.

The second design effect ( $d_r$ ) attributable to repeated evaluations (baseline/endline) is calculated by using the within ICC and a cluster autocorrelation coefficient ( $\pi$ ) of 0.80.

The second design effect ( $d_r$ ) is calculated as:

$$d_r = (1 - r^2)$$

Where  $r = \left( \frac{m\rho\pi}{d_c} \right)$

The required sample size is then calculated by multiplying the ‘sample size assuming individual randomization’ by both design effects ( $d_c$  &  $d_r$ ). It is calculated as:

$$n = \left[ \frac{(a+b)^2 * (p_1 q_1 + p_2 q_2)}{(p_1 - p_2)^2} \right] * d_c d_r$$

Where:

$n$  represents the sample size in each of the arms i.e., intervention and control

$a$  represents conventional multiplier (1.96) for alpha ( $\alpha = 0.05$ ) and  $b$  represents conventional multiplier (0.842) for power ( $1 - \beta = 0.80$ )

$p_1$  represents proportion of post-intervention users of MWH and  $q_1$  represents proportion of post-intervention non-users of MWH.

$p_2$  represents proportion (50%) of users of MWH taken from a study in Gurage Zone, Southwest Ethiopia  and  $q_2$  represents pre-intervention proportion of non-users of MWH.

$|p_1 - p_2|$  *an effect size* - is an absolute change in proportion of MWH utilization after intervention. It is estimated to be 20%.

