In addition, the following parameters are considered: 95% CI, 80% power, 1:1 allocation ratio of intervention to control, 10% potential loss to follow up, and tabulated sample size ( $n_0 = 199$ ) required to detect a difference in two proportions at 5% significance level with 80% power in literature.  According to Hooper and Bourke, the number of clusters (K) for the sample is determined using the formula  $K = (n_0 d_c d_r) / m$ . The final sample size is calculated by substituting the specified values into the above formula. Hence, a total of 16 clusters are needed, with an approximated final sample size of 320 couples. The two arms each will have 160 couples (pregnant women with their male partners).

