### **Eligibility criteria**

The study participants will be couples living together where the women are pregnant in the beginning of second trimesters of pregnancy (14-16 weeks of gestation) and had given birth in the last 5 years before the current pregnancy, permanent residents of the study area, living  $\geq 2$  hours of walking distance from the nearest health facility and/or have no or limited access to public transportation, and are willing to participate in the study.

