### **Statistical analysis**

The data analysis will be performed using STATA or SPSS software. The outcome variables will be computed at baseline and endline for both intervention and control groups. The outcome measures between the intervention and control arms will be compared using the Pearson's chi-square test of independence. The difference-in-difference (diff-in-diff) estimator will be used to estimate the effect of the intervention. Furthermore, we will perform generalized linear model regressions to determine the odds of outcomes between the intervention and control groups. The data will be analyzed using an intention-to-treat approach. The statistical significance will be declared at  $p\text{-value} < 0.05$  with 95% confidence interval.

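### The sample size takes the variance saving of a baseline-adjusted analysis, but the primary effect is a difference-in-differences, so the stated 80% power does not belong to the stated estimator

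*Protocol*

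**What the plan says.** The Primary outcome section computes the proportion using a maternity waiting home (MWH) in each arm at baseline and endline, then states: "The effectiveness of the intervention will be measured as a difference-in-differences in the proportion of MWH use between the trial arms". The Protocol summary says the same. The Statistical analysis section repeats that a difference-in-difference "estimator will be used to estimate the effect of the intervention". It adds a generalized linear model for odds, with no baseline term named.

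The Sample size calculations section multiplies the individually randomised sample size by two design effects. The second is said to be "attributable to repeated evaluations (baseline/endline) is calculated by using the within ICC and a cluster autocorrelation coefficient" of 0.80. It is d_r = 1 - r², with r = mρπ/d_c. The method is described as one for repeated cross-sections.

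Three other sections bear on this:
- **Eligibility criteria:** women enter at 14-16 weeks and must have "had given birth in the last 5 years before the current pregnancy".
- **Description of important terms and measurement:** an MWH stay belongs to the final 2-3 weeks of gestation.
- **Sampling procedure:** the women assessed at baseline are the ones assessed again at endline.

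**The concern.** The protocol fixes both the estimator and the variance factor, and they belong to different analyses. Adjusting for baseline and subtracting baseline are not interchangeable. Adjustment gives baseline the weight that its correlation with endline supports. Subtraction forces that weight to 1. When r is moderate, as the protocol assumes, subtraction costs precision. The trial could then run with less power for its declared primary effect than the 80% on which it was justified.

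The nature of the baseline adds to this. A woman at 14-16 weeks has not reached the stage at which an MWH stay takes place, so her baseline MWH use can only concern an earlier birth. The protocol does not say so outright, but its timings leave no other reading. That variable is a reasonable covariate. It is not a pre-period value of the index-pregnancy outcome, which is what a difference-in-differences presumes.

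**Working it through.** **Inputs (Sample size calculations section).** "conventional multiplier (1.96) for alpha"; "conventional multiplier (0.842) for power"; p2 "represents proportion (50%) of users of MWH taken from a study in Gurage Zone, Southwest Ethiopia"; effect 20 points, so p1 = 0.70; ρ = 0.05; m = 20; π = 0.80; n0 = 199; and "95% CI, 80% power, 1:1 allocation ratio of intervention to control, 10% potential loss to follow up".

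**Step 1: reproduce the plan.**
- d_c = 1 + 19 × 0.05 = 1.95
- r = 20 × 0.05 × 0.80 / 1.95 = 0.410
- d_r = 1 - 0.410² = 0.832
- K = 199 × 1.95 × 0.832 / 20 = 16.1 clusters, against 16 stated.
- By the formula: (1.96 + 0.842)² × (0.21 + 0.25) / 0.2² = 90.3 per arm; × 1.95 × 0.832 = 146.4; / 0.9 for loss = 162.7, against 160 stated.

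The stated size therefore rests on 1 - r².

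**Step 2: which analysis each factor describes.** For Kebele means with equal variance at both times and correlation r, endline minus b × baseline has relative variance 1 + b² - 2br.
- b = r (covariate adjustment) gives 1 - r² = 0.832.
- b = 1 (difference-in-differences) gives 2(1 - r) = 1.179.
- b = 0 (endline only) gives 1.

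The ratio 1.179/0.832 is 1.42. The gap is 2(1 - r) - (1 - r²) = (1 - r)², which is never negative.

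**Step 3: power on the protocol's inputs.** SE² = 0.46 × d_c × factor / N per arm; power = Φ(0.2/SE - 1.96). After 10% loss, N = 144 and m = 18, so d_c = 1.85, r = 0.72/1.85 = 0.389, and the factors are 0.849 and 1.222.

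| Analysis | 160 per arm: SE, power | 144 per arm: SE, power |
|---|---|---|
| Baseline-adjusted | 0.0683, 83% | 0.0708, 81% |
| Endline only | 0.0749, 76% | 0.0769, 74% |
| Difference-in-differences | 0.0813, 69% | 0.0850, 65% |

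For 80% power, difference-in-differences would need 90.3 × 1.95 × 1.179 = about 208 evaluable per arm. That is 231 with 10% loss, or about 12 clusters per arm instead of 8.

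**Step 4: within-woman correlation τ (assumed; the documents give none).** With the same women measured twice, r = (mρπ + (1 - ρ)τ)/d_c. Power of difference-in-differences after loss:

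| τ | 0 | 0.1 | 0.2 | 0.3 | 0.36 |
|---|---|---|---|---|---|
| Power | 65% | 69% | 73% | 78% | about 80% |

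At τ = 0.2 the baseline-adjusted analysis has 85%.

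**Step 5: unequal variances (baseline use assumed; τ = 0, 144 per arm).** The 2(1 - r) factor presumes equal variance at the two times. Using V_end + V_base - 2r√(V_end × V_base) in each arm, with endline at 50% and 70%:

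| Baseline use | Variance relative to endline only | Power |
|---|---|---|
| 50% | 1.28 | 63% |
| 20% | 1.05 | 72% |
| 10% | 0.91 | 78% |

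**Step 6: few clusters.** Against a t reference with 14 df (16 clusters), power after loss is about 75% for the adjusted analysis and about 59% for difference-in-differences.

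**The case against.** The best defence is that 65% treats a cohort as repeated cross-sections. The same women are interviewed twice, so r may well exceed 0.41, and at τ of about 0.36 difference-in-differences recovers the planned power. Low baseline use would help as well, and the protocol itself describes MWH use in this zone as low. All of this stands, and it rules out a flat 65%.

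Three further readings are tempting but not supported:
- **That difference-in-differences is simply noisier than ignoring baseline.** With equal variances this holds only while r < 0.5, that is, τ below about 0.18 with 20 women per Kebele. With 10% baseline use it fails even at τ = 0.
- **That the autocorrelation of 0.80 is too high because baseline refers to an earlier birth.** The inference about the baseline is sound, but no figure in the documents shows what the correlation would be.
- **That the estimator is biased or inflates type I error.** Under randomisation the choice between subtraction and adjustment does not by itself do so. The loss is in efficiency and in the accuracy of the power statement.

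It can also be said that the difference-in-differences might be fitted with covariates, and that model terms are commonly left to an analysis plan not shown here. The protocol does not exclude this. But it states the effect measure and the variance factor itself, and the two disagree as written.

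**Conclusion.** The mismatch stands. The 80% power belongs to a baseline-adjusted analysis that the protocol does not name. For the named estimator, the protocol's own inputs give about 69% with 160 per arm and about 65% after 10% loss, a shortfall of some 15 points against adjustment (83% and 81%). This rests on r = 0.41, equal variances at the two times, no within-woman correlation and normal quantiles. Over the scenarios worked through, the figure after loss runs from 63% to about 80%, so a reader should not take 65% as the trial's actual power. What needs no assumption about τ or π, given equal variances, is that adjustment is at least as efficient at every r. Separately, baseline MWH use comes from an earlier birth and is a covariate rather than an earlier reading of the primary outcome. Adjustment makes d_r match the analysis, but it does not by itself secure 80% once a 14-df reference is used.

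**What to change.** In the Protocol summary, Primary outcome and Statistical analysis sections:
- Define the primary outcome as MWH use in the index pregnancy, measured at endline.
- Estimate the between-arm difference in a model that accounts for Kebele and adjusts for MWH use at the last birth, entered as the woman's own value and the Kebele proportion.
- Label the baseline variable as MWH use at last birth.
- Report the difference-in-differences as descriptive or supportive.

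If difference-in-differences stays primary, restate its power in the Sample size calculations section as about 65-69% under the protocol's inputs, with the range over within-woman correlation and baseline use.

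Either way, note that 16 clusters with a 14-df reference lower the figures further.

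The change uses data the baseline questionnaire already collects and needs no more participants. It does replace the primary estimator and requires the model to be written in. Under the Protocol amendment section it therefore needs ethics board approval before implementation.

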### **Secondary outcomes**

The couples knowledge and attitude will be measured at the baseline and endline (after the follow-up is completed). Consequently, the effect of the intervention on the participants' knowledge and attitudes will be compared between the trial arms.

### **Reliability of measures**

The data collection tool will be adapted from different studies such as Ethiopian Demographic Health Survey Documents, global framework for assessing male partners' involvement in maternal health and other relevant sources. The adapted tools will be structured to fit the study context, which contributes to the reliability of the measures. In addition, the reliability of the measurement items will be assessed using Cronbach's alpha and appropriate corrections will be made based on the test findings. The Cronbach's alpha cut-off value will be  $\geq 0.70$ . The data collectors will be trained on the standards and techniques of data collection.

### **Trial activity schedule**

The eligibility screening, obtaining informed consent, participant allocation, and baseline data collection will be performed in the months of September and October 2022. The actual intervention will be performed from November 2022 to April 2023. Then the endline data collection will be conducted two-weeks after the completion of the intervention, i.e., after May 15, 2023.

Accordingly, the participants' enrollment, intervention, and assessment schedule is summarized as follows (Table 3).

**Table 3:** Schedule of enrolment, interventions, and assessments

|               |                             |                        | STUDY PERIOD                            |                |                |                |                |                |                   |
|---------------|-----------------------------|------------------------|-----------------------------------------|----------------|----------------|----------------|----------------|----------------|-------------------|
|               |                             | Enrolment & Allocation | Post-allocation
(Intervention Phase) |                |                |                |                |                | Close out         |
| Time point    |                             | t (-1)      | t 1                          | t 2 | t 3 | t 4 | t 5 | t 6 | t (+1) |
| Enrolment     | Eligibility screen          |                        |                                         |                |                |                |                |                |                   |
|               | Informed consent            |                        |                                         |                |                |                |                |                |                   |
|               | Allocation                  |                        |                                         |                |                |                |                |                |                   |
| Interventions | Health Education + Leaflets |                        |                                         |                |                |                |                |                |                   |
|               | Home Visits + Leaflets      |                        |                                         |                |                |                |                |                |                   |
| Assessments   | Baseline data               |                        |                                         |                |                |                |                |                |                   |
|               | Knowledge & Attitude        |                        |                                         |                |                |                |                |                |                   |
|               | MWH utilization             |                        |                                         |                |                |                |                |                |                   |

### Sampling procedure

Sixteen clusters will be selected based on MWH availability in the area. These clusters will be randomly assigned to intervention and control groups. Census and/or health post records will be used to identify pregnant women in the chosen clusters, resulting in the formation of a sampling frame. The study participants will then be selected using a simple random sampling technique from the sampling frame. Each cluster will have 20 couples (20 wife-husband pairs). The same sample of participants assessed at baseline will be assessed at end line to measure the outcome (Figure 2).

